### Sample size calculations

We determined that the greatest threat to the feasibility is the ability to administer the first dose of study treatment in a timely fashion, within two hours of the first administration of furosemide. As such, it was selected as the outcome used to determine our sample size. Assuming an actual adherence of 92.5%, to demonstrate at least an 85% adherence, a sample size of 47 is required. Other important feasibility outcomes include the administration of 72 hours of study treatment to each patient, and the absence of hyperoncotic albumin administration in the control arm. Estimated sample sizes required to show those outcomes with the desired level of precision are shown in Table 
3.

### Data collection

Data to be collected are listed in Table 
4. Demographic information, prior medical conditions, and reason for admission to ICU will be recorded. The Acute Physiology and Chronic Health Evaluation (APACHE), and Sepsis-related Organ Failure Assessment (SOFA) will be used at the time of ICU admission, the time of randomization, and the treatment end. The administration and doses of intravenous fluids, blood products, and diuretics will also be recorded. Data related to rationale for diuresis will also be collected (peripheral edema, pulmonary edema on chest X-ray, low urine output, elevated central venous pressures or left atrial pressures). Study outcome data collected daily will include vital signs and hemodynamics (if central venous monitoring or pulmonary artery catheters are in place), fluid balance, hourly urine output, weight, ventilator settings (if patient is ventilated), intubation status (including reasons for intubation or re-intubation), oxygenation parameters (SaO_2_, FiO_2_, PaO_2_/FiO_2_ ratio, oxygenation index). Blood samples, to determine standard and extended electrolyte levels, renal profile, complete blood count with differential, serum albumin and total protein levels, and blood gas data, are routinely collected in patients undergoing diuresis and will be collected at least daily. Colloid osmotic pressure and serum total protein will also be assessed at baseline, day 3 and day 5. Study data will be collected from the time of ICU admission to hospital discharge or 30 days after enrollment. All of these data are measured routinely in the ICU and subject to minimal interobserver variation. Colloid osmotic pressure will be measured using the Wescor model 4220, which has a precision of ± 0.03 mmHg
[21].

Subject data will be collected daily through examination of the patient chart, including electronic ICU charting and the Meditech laboratory reporting system. Standardized electronic case report forms will be used to collect patient and study data. Data recording will be performed using standardized case report forms in duplicate to ensure minimal human error. Data from case report forms will be entered into an electronic database on a secure computer server. Given the short time of study treatment (3 days) and intensive follow-up to 5 days, retention of study subjects is not anticipated to pose a problem. Similarly, longer-term follow-up data for our outcomes of interest (transfer from ICU, ventilator-free days, and death) are easily retrieved from hospital records.

### Data management

Data will be entered using electronic case report forms into a computerized database stored on a secure server in the Department of Epidemiology and Biostatistics at McMaster University. All collected data will be kept under secure conditions in keeping with Good Clinical Practice and McMaster University’s research ethics board guidelines for a minimum of 7 years following study completion.

### Statistical methods

All *P* values will be two sided, with a level of *P* ≤ 0.05 indicating statistical significance. All data will be analyzed using statistical software on an intention-to-treat basis. All randomized participants, regardless of protocol adherence, will be included in the main analysis.

Feasibility outcomes will be calculated as proportions with 95% confidence intervals, with feasibility being met if the lower-bound of the 95% confidence interval is above the level pre-specified for feasibility (Table 
3). Data regarding our primary and secondary clinical outcomes will also be collected during this pilot study for future analysis; however, no analysis of clinical outcomes will be made for this pilot study, as the main purpose is to inform the definitive trial. Data collected from this pilot study will remain blinded and eventually incorporated into the dataset for the definitive trial, with the following pre-specified analyses.

Comparisons between the two treatment groups at a single time point (for example, baseline variables, number of patients requiring fluid bolus or vasopressors for hypotension, total dose of furosemide, and so on) will made using unpaired Student’s *t* test. Comparisons within a treatment group at different time points (change in serum albumin, colloid osmotic pressure, total protein, weight, fluid balance, oxygenation, lung compliance at day 3 and day 5, and so on) will be analyzed in a similar fashion. Multiple between-groups comparisons of continuous variables will be analyzed by repeated-measures analysis of variance. Linear regression will be used where appropriate to correct for baseline variables. Ventilator-free days will be defined as the number of 24-hour periods in which a patient does not need ventilation during 28 days (patients who die, by definition, will have 0 ventilator-free days). Survival analysis will be performed to assess 30-day mortality.

*A-priori* analyses include stratifying patients by illness severity at time of randomization (using APACHE and SOFA scores), presence of ARDS, patients admitted with sepsis, patients admitted with congestive heart failure, and time since recovery of hemodynamic stability (greater than or less than 48 hours from discontinuation of vasopressors). All subgroups carry biological plausibility for differing effects of the intervention, with the hypothesis of greater improvement in those patients with more severe illness, presence of ARDS, and shorter time since hemodynamic stability.

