**Methods/Design:**

FADE is a single-center, parallel, pilot randomized controlled trial. We aim to allocate 50 hemodynamically stable, hypoalbuminemic adult patients receiving diuresis to treatment with either 100 ml of either 25% albumin or normal saline placebo twice daily, for a total of six doses. Diuretics are to be prescribed by the caregiving team at least twice daily, and administered within 2 hours following study treatment. Patients, intensive care unit (ICU) clinicians, data collectors, and outcome adjudicators will be blinded to treatment allocation. Feasibility outcome measures include the proportion of patients receiving albumin within 2 hours of diuretic, the proportion of patients receiving the full six doses of study treatment, the proportion of patients who receive open label 25% albumin, and the rate of recruitment. Physiologic, laboratory, and clinical data are collected until discharge from the ICU or until 30 days.

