Dose of furosemide	Lower total amount of furosemide used in treatment group at day 3	Dose of furosemide during 3 days of study treatment (mg)	None	*t* test
Changes in serum albumin	Greater increase in serum albumin level in treatment group at day 3 and day 5	Change in serum albumin (g/l)	None	*t* test
Changes in colloid osmotic pressure	Greater increase in colloid osmotic pressure in treatment group at day 3 and day 5	Change in colloid osmotic pressure (mmHg)	None	*t* test
Changes in serum total protein	Greater increase in total protein in treatment group at day 3 and day 5	Change in total protein (g/l)	None	*t* test
Change in electrolytes	No difference between study groups for major electrolytes (sodium, potassium) at day 3 and day 5	Change in electrolytes between beginning and end of study treatment (mEq/l)	None	*t* test

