### Randomization

The randomization process is outlined in Figure 
1. Participants will be randomly assigned to either the control or experimental group in a 1:1 fashion with allocation concealment using an online computer generated randomization schedule. Randomization will be done at the time that the treating physician judges diuresis to be necessary. Allocation of patients to the study group will be carried out by the transfusion medicine service, who will contact a web-based randomization system set up by the statistics team. The transfusion medicine personnel responsible for assignment are distinct from the study personnel enrolling subjects in the study in the ICUs. The transfusion medicine service will keep an electronic list of patient names, study ID numbers, and treatment allocation. Study investigators will not have access to this list and will have to contact the transfusion medicine service to unblind patients for any reason, for example, suspected adverse reaction to a study treatment.

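### The Statistical methods text conflicts with Table 2 on how change outcomes, a yes/no outcome and electrolytes are tested, and seven Table 2 rows leave out the baseline value

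*Protocol article*

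**What the plan says.** Statistical methods gives one test for comparing the arms at a single time point. Its examples include a count of patients: "number of patients requiring fluid bolus or vasopressors for hypotension, total dose of furosemide, and so on) will made using unpaired" Student's t test. The next sentence turns to change over time: "Comparisons within a treatment group at different time points (change in serum albumin, colloid osmotic pressure, total protein, weight, fluid balance, oxygenation", together with lung compliance, at day 3 and day 5. It says these will be analysed in like manner, and no paired test is named anywhere. The same section allows linear regression to correct for baseline where appropriate, without naming outcomes, and repeated-measures analysis of variance for multiple between-group comparisons.

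Table 2 treats the same variables as comparisons between arms, for example "Greater increase in serum albumin level in treatment group at day 3 and day 5". Its covariate and method columns differ by row:

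- Fluid balance and body weight: baseline value as covariate; t test and linear regression.
- PaO2/FiO2, oxygenation index, dynamic compliance, serum albumin, colloid osmotic pressure, total protein and electrolytes: covariates None; t test only.
- Dialysis (yes/no): chi-squared or Fisher's exact.

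The electrolyte hypothesis in Table 2 is "No difference between study groups for major electrolytes (sodium, potassium) at day 3 and day 5", measured as change in mEq/l. The Outcomes section describes the electrolyte outcome by limits: potassium below 2.5 or sodium above 150 mEq/l.

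These analyses are meant for the definitive trial's dataset. Statistical methods says the pilot will not analyse clinical outcomes, and the Dissemination policy allows results by arm only if non-feasibility is found.

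**The concern.** Two parts of one plan give different analyses for the same outcomes, and an analyst would have to choose between them. The literal text leads to an unpaired test on before-and-after values from the same patients. Even a paired version would not answer Table 2's question. Both arms are selected for low albumin or total protein and for a decision to diurese, so values may move in both arms whatever albumin does.

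Three smaller matters sit beside this. Seven Table 2 rows compare change without the baseline value, which gives away precision. A t test is named for a yes/no outcome although Table 2 uses a test for proportions for dialysis. The electrolyte outcome, meant as a check on harm, is planned as a test of mean change whose hoped-for result is no difference. A mean can stay put while a few patients cross a harmful limit, and a non-significant result is weak evidence of safety.

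**Working it through.** **The plan's own figure.** The sample size rests on a feasibility proportion: "Assuming an actual adherence of 92.5%, to demonstrate at least an 85% adherence, a sample size of 47 is required". With n = z²p(1−p)/d², z = 1.96, p = 0.925 and d = 0.075:

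1.96² × 0.925 × 0.075 / 0.075² = 47.4, against 47 stated.

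The figure reproduces and uses none of the tests discussed here.

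**Inputs.** Two-sided 5% level (Statistical methods); 50 patients (Abstract) allocated 1:1 (Randomization), so 25 per arm. The documents give no correlation r between baseline and follow-up. I assume 0.3 to 0.8, equal variances at the two times, and a shift of 0.5 SD for illustration.

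**1. Unpaired test on within-arm change.** The variance of a mean change is proportional to 2(1−r), and the unpaired test uses 2. Its standard error is therefore too large by 1/√(1−r), and its true size is about 2P(Z > 1.96/√(1−r)). At r = 0.5 the factor is 1.41 and the size is 2P(Z > 2.77) = 0.6%. Simulation with 25 patients and 40,000 runs gives:

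| r | SE factor | Size, unpaired | Power, unpaired | Power, paired |
|---|---|---|---|---|
| 0.3 | 1.20 | 2.1% | 40% | 53% |
| 0.5 | 1.41 | 0.7% | 38% | 67% |
| 0.7 | 1.83 | 0.1% | 35% | 87% |

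The paired test stays at about 5% throughout.

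**2. Between-arm change without baseline.** The per-patient variance is 2(1−r) for the change score and 1−r² for ANCOVA, a ratio of (1+r)/2. The number per arm for 80% power is 2(1.96+0.84)² × variance / 0.5²:

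| r | Variance ratio | n per arm, change score | n per arm, ANCOVA |
|---|---|---|---|
| 0.3 | 0.65 | 88 | 58 |
| 0.5 | 0.75 | 63 | 48 |
| 0.7 | 0.85 | 38 | 33 |
| 0.8 | 0.90 | 26 | 23 |

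The simulated size of the change-score t test at r = 0.5 is 4.9%, so it is valid.

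**3. The t test on a yes/no outcome.** Exact enumeration at 25 per arm gives the same size for the t test and Pearson chi-squared: 2.0%, 4.9%, 5.5% and 6.5% at event rates of 5%, 10%, 20% and 50%.

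**4. Electrolytes.** With 25 per arm and r = 0.5, the change score has an SD of 1. A true shift of 0.5 SD gives 0.5/√(2/25) = 1.77, so power is P(Z > 1.96 − 1.77), about 42% (32% at r = 0.3, 63% at r = 0.7). At r = 0.5 a real shift of that size would more often than not go undetected. This applies if the pilot's results were reported by arm; the size of the definitive trial is not given.

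**The case against.** The strongest reply is that Table 2 is the operative plan and is largely sound. Its directional physiologic hypotheses are between arms, the Outcomes section speaks of changes in albumin and colloid osmotic pressure between groups, and Statistical methods adds a between-group repeated-measures analysis. The sentence on change could then be a loose reference to a t test on each patient's change score, for which an unpaired test between arms is correct. That reading is possible, but the sentence says the comparison is within a treatment group, so the wording still has to be settled.

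A reader might infer that change outcomes in general are unadjusted, or that inference is invalid. The documents do not support either. Fluid balance and weight carry baseline covariates, and a between-arm t test on change keeps its size. The unpaired test on paired data errs on the cautious side when correlation is positive. The adjusted sensitivity analysis does not rescue the seven rows, however, because it uses the covariates as listed and these rows list none.

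A reader might also fear that ordinary recovery will be credited to albumin. If two identical arms each had 50% power to show change, albumin alone would be significant with probability 0.5 × 0.5 = 25%. That is the maximum of p(1−p), and it presumes an effect would be inferred from significance in one arm only. The plan nowhere says so.

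Nor does any sentence say that a non-significant electrolyte test will be reported as proof of safety. What stands is that the hypothesis, the test and the threshold definition do not match.

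**Conclusion.** The point holds as a conflict to reconcile and an avoidable loss of precision, not as a fault that overturns conclusions. Read literally, the within-arm test has a true size of about 0.6% at an assumed correlation of 0.5 and does not address the treatment effect. For the seven rows without a covariate, ANCOVA would have 0.65 to 0.85 of the variance at assumed correlations of 0.3 to 0.7, and the gain shrinks to 10% at 0.8. The yes/no t test is inconsistent with little numerical effect. The electrolyte mismatch is real because mean change does not measure the stated thresholds. All sizes rest on assumed correlations. The tests matter for the definitive dataset and for results by arm if non-feasibility is declared; no feasibility criterion uses them.

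**What to change.** - Rewrite the change sentence in Statistical methods to match Table 2: arms are compared, and within-arm change is descriptive only.
- For the Table 2 rows now marked None that concern change from baseline, compare arms by ANCOVA on the day 3 or day 5 value with the baseline value as covariate. Do this in patients with a baseline measurement: Data collection records ventilator settings only in ventilated patients, so compliance and oxygenation index will be absent for some.
- For hypotension needing fluid or vasopressors, use chi-squared or Fisher's exact with a risk difference.
- For electrolytes, report the proportion in each arm crossing the limits in the Outcomes section, and the between-arm difference, with 95% confidence intervals. Drop the no-difference test.

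The cost is analysis wording. The plan already collects the measurements, subject to the ventilator limit above. The article says recruitment has not begun, so the text can be settled before any data exist.

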The secondary clinical outcomes that we will collect data for include: (1) duration of mechanical ventilation, measured from time of randomization until extubation that is successful for 24 hours or more, recorded in days; (2) number of episodes of interrupting treatment with furosemide (for example, hypotensive episodes, renal failure, contraction alkalosis); (3) proportion of patients receiving dialysis; (4) length of ICU stay from randomization; (5) ICU mortality; and (6) 30 day mortality. We hypothesize that the addition of 25% albumin will lead to fewer interruptions of diuresis, a reduced incidence of acute kidney injury, and a shorter stay in the ICU.

The secondary physiologic outcomes that we will collect data for include: (1) changes in oxygenation (FiO_2_, PaO_2_/FiO_2_ ratio, oxygenation index) from baseline at day 3 and day 5; (2) changes in dynamic lung compliance, reflecting changes in extravascular lung water, at day 3 and day 5; (3) changes in total fluid balance and body weight, and amount of urine output from baseline at day 3 and day 5; (4) total dose of furosemide used, to assess whether study treatment improves the physiologic response to furosemide; (5) changes in serum albumin and colloid osmotic pressure between treatment groups from baseline at day 3 and day 5, to ensure that the experimental treatment results in the expected increases in these measurements; (6) changes in electrolyte levels (potassium level less than 2.5 mEq/l, sodium level >150 mEq/l), as a way to ensure that no major, potentially harmful changes in serum electrolytes occur as a result of study treatment.

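### Repeated-measures ANOVA in its classical form needs a complete series for every patient, which sits badly with the promise to include all randomized participants and may cost precision and bias the comparison

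*Protocol article*

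**What the plan says.** The Statistical methods section of the protocol article lists analyses pre-specified for the definitive trial, into which the pilot data will be carried. Among them: "Multiple between-groups comparisons of continuous variables will be analyzed by repeated-measures analysis of variance". It names no outcome, covariance form or rule for incomplete patients. The same section says: "All randomized participants, regardless of protocol adherence, will be included in the main analysis".

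Other parts of the article bear on the point:

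- **Eligibility (Participants).** Patients expected to survive, or to stay in the ICU, for less than 72 hours are excluded. Nothing requires a stay to day 5, and ventilation is not an inclusion criterion.
- **Time points (Outcomes, Tables 2 and 4).** Most physiologic outcomes are changes from baseline at day 3 and day 5, for example "changes in dynamic lung compliance, reflecting changes in extravascular lung water, at day 3 and day 5". Many variables are recorded on each of days 1 to 5.
- **End of collection.** The abstract says: "Physiologic, laboratory, and clinical data are collected until discharge from the ICU or until 30 days". The Data collection section instead continues to hospital discharge or 30 days.
- **Methods by outcome (Table 2).** Every day-3 and day-5 outcome has a t test, some with linear regression. None has repeated-measures ANOVA.
- **Use in the pilot.** Statistical methods says "no analysis of clinical outcomes will be made for this pilot study". The Dissemination policy allows outcomes by treatment group to be published if non-feasibility is shown.

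**The concern.** A patient who leaves the ICU, is extubated or dies after day 3 may have no day-5 value for some or all outcomes. Classical repeated-measures ANOVA then removes that patient entirely, including the values already recorded on days 1 to 3. The remaining patients are selected after randomization, so they are no longer the randomized groups that the section promises to compare.

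Two things are at stake. Precision falls because observed data go unused. The comparison may also be distorted. The article itself hypothesizes better oxygenation, more ventilator-free days, a shorter ICU stay and lower mortality with albumin. If those hypotheses are right, the patients still measured at day 5 differ between arms because of the treatment.

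**Working it through.** **The plan's own figure.** The article gives no sample size, power or missing-data rate for this analysis. Its only sample-size basis is first-dose adherence: n = 1.96² × 0.925 × 0.075 / 0.075² = 47.38, against the stated 47. It reproduces but does not bear on this point.

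**Inputs.** From the abstract, 50 patients; from Randomization, "either the control or experimental group in a 1:1 fashion", so about 25 per arm. Tests are two-sided at 0.05. The share of incomplete patients, m, is an assumption: 10% to 40%.

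**Precision.** If only complete patients are used, the interval width is multiplied by 1/√(1 − m). A nominal 80% power becomes Φ[(1.960 + 0.842)√(1 − m) − 1.960].

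| m | Complete of 50 | Width factor | Power |
|---|---|---|---|
| 10% | 45 | 1.05 | 76% |
| 20% | 40 | 1.12 | 71% |
| 30% | 35 | 1.20 | 65% |
| 40% | 30 | 1.29 | 58% |

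The reference is a trial with no missing values. A mixed model regains only part of this loss, so these figures are upper bounds on the gain from changing method.

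**Bias.** This was checked by simulation with 400,000 patients per arm and five daily values with SD 1. The true treatment difference rose linearly from 0 on day 1 to 0.5 SD on day 5. Patients left after day 3 or day 4 when their last value was good; in one variant, also when it was very poor. All these settings are assumptions.

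| Correlation between days | Incomplete, control / treated | Quantity | True | Complete cases | Likelihood, all observed |
|---|---|---|---|---|---|
| Equal, 0.7 | 12–39% / 20–51% | Change, day 1 to 5 | 0.50 | 0.50 | 0.50 |
| Equal, 0.7 | same | Level on day 5 | 0.50 | 0.33–0.41 | 0.50 |
| AR(1), 0.8 | 11–34% / 18–47% | Change, day 1 to 5 | 0.50 | 0.45–0.48 | 0.50 |
| AR(1), 0.8 | same | Mean over days 1–5 | 0.25 | 0.10–0.16 | 0.25 |

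With no treatment effect and the same leaving rule in both arms, the complete-case bias was zero to simulation error in both settings.

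Three points follow:

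- The mean over days is what the between-group main effect of a repeated-measures ANOVA estimates, and it was the most attenuated quantity.
- Under equal correlation the change score escapes, because selection on the day-3 or day-4 value shifts the day-1 and day-5 means equally.
- No one returned after leaving, so patients with a day-5 value are exactly the complete cases. The day-5 change results therefore apply equally to a day-5 t test on change among those observed.

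**The case against.** The strongest objection is that deletion is inferred. A reader might take the plan to say that incomplete patients are dropped, but no sentence says so. It follows from the classical form of the named method, and handling of missing values is something an article may leave to a fuller document. This stands as a limit on the wording. The point survives because the article names a method whose usual form contradicts a promise in the same section.

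Table 2 gives t tests or regression to every day-3 and day-5 outcome. So a reader should not infer that the day 1 to 3 data of early leavers would be lost from the analyses listed there; a day-3 t test would keep them. This stands too, and it leaves the role of the ANOVA unclear. A day-5 t test would still lose patients without a day-5 value.

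A reader of the abstract alone might infer that measurement always stops at ICU discharge. The Data collection section contradicts that. However, it records ventilator settings only in ventilated patients, so dynamic compliance would be missing after extubation wherever the patient is, and the dead have no later values under either statement.

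It is also tempting to say that the comparison will be biased. The simulations do not support that: there was none under the null with equal leaving rules, and none for change scores under equal correlation. Leaving depended on observed values only, so the likelihood method's success was built in. Deaths were not modelled as such.

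Finally, the pilot's feasibility outcomes are untouched. The clinical and physiologic analyses are reserved for the definitive trial, unless non-feasibility leads to publication by group.

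**Conclusion.** The point holds in a conditional form and is of low urgency. The named method, as classically applied, is consistent with analysing all randomized participants only if nobody has a missing value, and the design makes missing values between day 3 and day 5 foreseeable.

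The loss of precision is at most 5% to 29% in interval width, resting on an assumed 10% to 40% incomplete. Bias is possible if departure depends on the outcome and the treatment works. It ran toward zero wherever it appeared in the simulations, with a size that depended on the correlation between days and the quantity estimated. The consequence falls mainly on the definitive trial. It reaches the pilot only if results by group are published after non-feasibility, when 10% to 40% incomplete would leave 45 to 30 of 50 patients.

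**What to change.** Replace the repeated-measures ANOVA sentence with wording such as:

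> Continuous outcomes measured on several days will be analysed with a likelihood-based linear mixed model for repeated measures, using all observed values from all randomized participants, with treatment, day, treatment-by-day and baseline value as fixed effects. The estimates of interest are the treatment differences at day 3 and day 5.

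In addition:

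1. Align Table 2, so that the day-3 and day-5 outcomes now given t tests use this model.
2. Report the number observed per arm on each day.
3. Reconcile the abstract with the Data collection section on whether collection ends at ICU or hospital discharge.
4. State the missing-at-random assumption. Describe deaths, and ventilator-derived measures after extubation, separately by arm, because the model does not resolve what those values would mean.

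The cost is a change of analysis wording and standard software, with no change to sample size or conduct; item 3 only settles which existing statement applies. The price is the missing-at-random assumption, which the data cannot verify.
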